### Outcomes

AHI and ESS will be the primary outcomes. Secondary outcomes will be Oxygen Desaturation Index, Snoring Index, Pittsburgh Sleep Quality Index, Manual Assessment Of Respiratory Motion, Breath Hold Test, and Self Evaluation of Breathing Questionnaire.

#### Home sleep apnea testing (HSAT)

Home sleep apnea testing will be used to diagnose and measure severity of OSA as recommended by the American Sleep Disorders Association (ASDA) [20, 21]. According to Sleep, Cardiovascular, Oximetry, Position, Effort, and Respiratory (SCOPER) parameters, the HSAT that will be used can be denoted as denoted as S_0_, C_3_, O_1X_, P_2_, E_1_, and R_2_ [22]. HSAT has a high sensitivity (82%), specificity (88%), and positive predictive value of (89%) [21, 23].

The parameters measured are as follows:Apnea Hypopnea Index (AHI)—the average number of events of apnea and hypopnea per hour during sleep. AHI is used to determine the severity of OSA as mild (AHI 5 up to 15), moderate (AHI 15 up to 30), and severe (AHI 30 or more).Oxygen Desaturation Index (ODI)—the average number of episodes of oxygen desaturation per hour.Snoring Index (SI)—the measure of number of snoring events per hour during sleep.

#### Epworth Sleepiness Scale (ESS)

The ESS is a self-administered questionnaire used to measure the level of daytime sleepiness of a subject. The ESS consists of 8 items which are rated on a scale of 0 (no chance of dozing) to 3 (high chance of dozing) yielding a total score ranging from 0 to 24. The scale has test–retest reliability (Pearson’s correlation coefficient, *r* = 0.82), high degree of internal consistency (Cronbach’s *α* = 0.88) and validity [24].

#### Pittsburgh Sleep Quality Index (PSQI)

The PSQI is used to assess the quality of sleep and disturbances during sleep. The PSQI is a reliable and valid self-rated questionnaire. PSQI consists of 9 items that are divided into 7 components. For scoring, these 7 components are each scored from 0 (no difficulty) to 3 (severe difficulty) summing to produce a global PSQI score ranging from 0 to 21, with higher scores indicating declining sleep quality. The scale has a high degree of internal consistency (Cronbach’s *α* = 0.83), good test–retest reliability (Pearson’s correlation coefficient, *r* = 0.85), and validity [25].

#### Manual Assessment of Respiratory Motion (MARM)

The MARM is reported to be a valid and reliable tool for clinical and research purposes [26], used to evaluate and quantify breathing patterns with respect to the ribcage and abdominal movement. The volume, balance, and percentage of ribcage motion will be recorded.

#### Breath Hold Test (BHT)

The Breath Hold Test is a reliable and valid method to assess biochemical component of breathing dysfunction [27, 28]. Three maximal breath holds will be performed at 3-min rest intervals each. The mean of three readings will be used to determine the results.

#### Self Evaluation of Breathing Questionnaire (SEBQ)

The SEBQ is a self-reported outcome measure to determine breathing related symptoms. The SEBQ has 25 items, each scored from 0 (never/not true at all) to 3 (frequently/very true). A total score greater than 11 shows that the individual has a breathing problem. The SEBQ has a high test–retest reliability [intraclass correlation coefficient (3, 1) = 0.89; 95% CI 0.85–0.92], internal consistency (Cronbach’s *a* = 0.93), and validity [29].

### Data monitoring and management

Proper execution of the research and its progress’ responsibility will be the responsibility of the principal investigator. The data monitoring and safety committee (DMSC) will check for the accuracy of the data and participants’ safety. The research progress will be updated with the DMSC through regular meetings every 6 months. Participants will be informed to report any adverse event to the investigator. Collected data will be stored in secured cabinets. Microsoft excel will be used to store the participants’ deidentified data. The number of participants not adherent to the study, withdrawals, and those who are lost to follow-up will be noted along with the reasons.

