### Randomization, allocation, and blinding

The randomization will be done using computer-generated block randomization. Allocation will be done using sealed envelopes. The allocation sequence will be kept safely in “sequentially numbered opaque sealed envelopes.” The eligible participants will be informed about the trial process by the principal investigator and an informed consent will be sought. A blinded assessor will collect outcome measures at baseline, at the end of 12 weeks, and at the end of 24 weeks. The treatment will be given to the participant by the therapist according to that mentioned in the sealed envelope.

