#### Diaphragmatic breathing exercise [18]

This exercise will be performed 5 times by the subject.

This protocol will be followed 3 times per day for 5 days per week for 12 weeks. The treatment will be supervised for the 1st week. From the 2nd week, weekly supervised sessions will be held with the participants. A weekly exercise diary will be provided to the patients to document their adherence to treatment.

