#### MFT group: myofunctional therapy + CPAP

The myofunctional therapy will include the oropharyngeal exercises of soft palate, tongue, and face as outlined above. Myofunctional therapy will be performed 3 times per day, 5 days per week for 12 weeks.

CPAP treatment will be given to the subjects daily in both the groups for 12 weeks. The CPAP prescription will be followed as directed by the pulmonologist. CPAP data will be noted to record compliance. Compliance will be defined as use of the CPAP for ≥ 4 h per night for at least 70% of nights in the 12 weeks will be followed [19].

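### The only adverse event route the article states is spontaneous reporting, and supervised sessions and a diary are stated only for the CR arm; harms are likely to be under-recorded and may be recorded unevenly

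*Protocol article*

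**What the plan says.** On safety, the section on data monitoring and management gives one collection rule: "Participants will be informed to report any adverse event to the investigator". The same section gives the oversight: "The data monitoring and safety committee (DMSC) will check for the accuracy of the data and participants’ safety", with six-monthly meetings. It does not say which safety data the committee receives.

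On contact with participants, the CR arm description, under the diaphragmatic breathing heading, states "The treatment will be supervised for the 1st week", then "From the 2nd week, weekly supervised sessions will be held with the participants", and also "A weekly exercise diary will be provided to the patients to document their adherence to treatment". The purpose given for that diary is adherence, not adverse events.

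The MFT arm description refers back to the CR text for the exercises and then gives the schedule: "Myofunctional therapy will be performed 3 times per day, 5 days per week for 12 weeks". It says nothing about supervision or a diary.

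Contacts that clearly apply to both arms are in the section on randomization, allocation and blinding: "A blinded assessor will collect outcome measures at baseline, at the end of 12 weeks, and at the end of 24 weeks".

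**The concern.** Spontaneous reporting depends on the participant recognising an event, thinking it worth mentioning and having an occasion to mention it. It tends to miss events, especially minor or expected ones. The article commits to this method although both arms already have two scheduled post-baseline contacts at which a standard question could be asked.

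The second issue is the written difference between arms. Regular supervised sessions give repeated occasions to volunteer an event, and they are written only into the CR arm. CR is also the only arm that receives functional nasal breathing rehabilitation and diaphragmatic breathing. If contact does differ as written, the chance of recording an event is tied to the components under test. An excess of events in CR could then reflect more reporting rather than more harm, and a lack of events in MFT could reflect fewer occasions to report.

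What is at stake is the committee's check on participant safety and whatever the final report says about harms by arm. The efficacy analysis is not affected.

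**Working it through.** No stated figure is in dispute, so there is nothing to reproduce. The check compares sections of the text and adds a short count of sessions.

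**1. Is any active route stated?** The monitoring section tells participants to report. The assessor's task at baseline, week 12 and week 24 is to collect outcome measures, and the Outcomes section lists no harms among them. The Self Evaluation of Breathing Questionnaire records breathing symptoms in both arms, but it is a secondary outcome and is not described as a source of adverse events. So spontaneous reporting is the only route stated. Other routes are not excluded.

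**2. Is contact stated equally?**

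| Item | CR arm | MFT arm |
|---|---|---|
| Schedule: 3 times a day, 5 days a week, 12 weeks | stated | stated |
| Supervision in week 1 | stated | silent |
| Weekly supervised sessions from week 2 | stated | silent |
| Weekly exercise diary | stated | silent |
| Daily CPAP with compliance data | stated for both | stated for both |
| Therapist gives the allocated treatment | stated for both | stated for both |
| Assessor at baseline, weeks 12 and 24 | stated for both | stated for both |

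The MFT text repeats the schedule in full but not the supervision or the diary. A difference in contact is therefore a fair reading, though not the only one.

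**3. How much of the exercise is supervised?** The schedule gives 3 × 5 × 12 = 180 sessions per participant in each arm. For CR, two quantities are not fixed: how many week 1 sessions are supervised, and how many supervised sessions there are in each later week.

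- Assume all of week 1 (3 × 5 = 15) and one session in each of weeks 2 to 12 (11): 15 + 11 = 26 supervised, 26/180 = 14.4%, leaving 154 unsupervised.
- Assume one session on each of the 5 days in week 1 and one a week after that: 5 + 11 = 16, 16/180 = 8.9%, leaving 164 unsupervised.
- Assume all of week 1 and two sessions a week after that: 15 + 22 = 37, 37/180 = 20.6%, leaving 143 unsupervised.

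Under each assumption about four fifths or more of CR sessions have nobody present to notice or ask about an event. The MFT figure cannot be computed because its supervision is not described.

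**4. When would capture be uneven?** Let the true event risk be p in both arms and the probabilities that an event is recorded be c(CR) and c(MFT). The recorded risks are p·c(CR) and p·c(MFT). Their difference is p·[c(CR) − c(MFT)] and their ratio is c(CR)/c(MFT). If the two probabilities are equal but below 1, both counts are too low and the ratio stays at 1. Distortion between arms needs unequal capture. The document gives neither probability, so no size can be attached.

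**The case against.** The strongest reply is that this is a condensed article. Adverse event forms and a schedule of enquiry are commonly left to the full protocol, and telling participants to report events does not rule out asking them as well. The MFT paragraph may also simply be abbreviated. A therapist gives the allocated treatment in both arms, CPAP data are recorded in both, and non-adherence, withdrawals and losses are noted with reasons without restriction by arm. In addition, harms are not an outcome, and the planned analysis contains no comparison of harms between arms.

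Much of this stands. A reader might infer that MFT participants have no staff contact between baseline and week 12, and that the comparison of harms is therefore bound to be biased. The documents do not support that. Silence on supervision is not a statement that there is none, therapist delivery is stated for both arms, bias needs unequal capture, and no formal comparison is planned. Any numerical risk ratio offered for the distortion would only be assumed capture rates divided by each other.

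The reply does not remove the method that is stated. The article chooses self-report as its adverse event rule and writes supervision and the diary into one arm only.

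A further objection concerns the remedy: a checklist specific to the exercises could reveal the arm to the blinded assessor, who also collects the manually assessed breathing measure. This is fair, and the fix has to allow for it.

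**Conclusion.** The point holds in limited form. The only adverse event route stated is spontaneous reporting, and supervised sessions and a diary are stated only for CR. Followed as written, under-recording is likely in both arms. More ready recording in CR is possible and depends on MFT contact actually being lower, which the article neither states nor excludes. The consequence falls on the safety committee's review and on any later description of harms by arm, not on the efficacy results.

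The supervised share of CR sessions, 14.4% at most with one supervised session a week from week 2 (8.9% to 20.6% across the assumptions shown), indicates how much depends on participants volunteering events. It does not measure bias. The conclusion assumes that the article's description of adverse event collection is what will be done. If the full protocol already provides identical scheduled enquiry in both arms, it is enough to say so.

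**What to change.** - State whether supervision and the diary are the same in both arms, so that the two intervention descriptions can be read together.
- Keep spontaneous reporting, and add the same active enquiry in both arms at the existing week 12 and week 24 contacts: one standard open question and a short arm-neutral checklist. If the assessor's blinding is at risk, have participants complete it themselves, or have unblinded staff already in the trial ask it.
- Put the same adverse event line in a weekly diary given to both arms, so that events during the 12 weeks do not depend on recall at week 12.
- Base any by-arm safety table, including one for the safety committee, on these identically collected data. List spontaneous reports and those elicited at supervised sessions separately.

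The cost is small. One form at two contacts for 118 participants is at most 118 × 2 = 236 forms. If the MFT arm has no diary at present, 59 participants would be given one. No visits or procedures are added. The downsides are that more minor events will be recorded and that a small unblinding risk must be managed through neutral wording or self-completion.

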## Results

Statistician will be provided deidentified data, and analysis will be performed. Descriptive statistics (frequency tables and percentages for categorical variables and for computation of prevalence) will be used.

Mean/median and standard deviation/inter-quartile range will be analyzed after exploring skewness for the quantitative variables. Repeated-measures ANOVA or its non-parametric variants will be used after exploring the model assumptions to assess the effectiveness of the intervention. Correlation analysis may be done to explore associations between the outcomes.

Regression models may be used for adjustment of covariates to account the confounding factors and for unbiased treatment effect. Intention to treat analysis will be used to manage missing data. Inferential statistics will be used for exploratory data analysis.

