**Methods:**

Patients diagnosed with OSA and meeting the eligibility criteria will be randomly allocated in the groups. The experimental group will receive comprehensive rehabilitation, and the control group will receive myofunctional therapy. CPAP will be continued by all the participants. Both the groups will receive the interventions for 12 weeks. The primary outcome measures are AHI and Epworth Sleepiness Scale (ESS), and secondary outcomes are Pittsburg Sleep Quality Index (PSQI), Oxygen Desaturation Index (ODI), Snoring Index (SI), Manual Assessment of Respiratory Motion (MARM), Breath Hold Test (BHT), and Self Evaluation of Breathing Questionnaire (SEBQ). The outcomes will be assessed at baseline and at the end of 12 weeks. A follow-up will be taken at the end of 24 weeks. Power analysis suggests that enrollment of 118 patients will required. Repeated measures ANOVA will be used to analyze the effect of the intervention.

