## Method

### Study design

The study design for the current protocol is an “assessor-blinded parallel group randomized controlled trial.” The trial will use the “Consolidated Standards of Reporting Trials (CONSORT) guidelines” [14]. All outcomes will be assessed at baseline and at the end of 12 weeks. Additionally, a follow-up will occur at the end of 24 weeks with assessment of daytime sleepiness, sleep quality, and breathing pattern dysfunction. The study flow is shown in Fig. 1. Reporting of the protocol is done according to the “Standard Protocol Items: Recommendations for Intervention Trials (SPIRIT) guidelines” [15]. The present study is approved by Institutional Research Committee (IRC) of Manipal Academy of Higher Education. Scientific Committee approval and ethical clearance to conduct the study is obtained from Manipal Hospital, Bangalore. The study is registered in Clinical Trials Registry–India (CTRI) (registration number—CTRI/2023/10/058486).

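### The primary analysis and its summary measure are chosen after looking at the outcome data, so the between-arm effect measure for AHI and ESS is not fixed in advance

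*Protocol article*

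**What the plan says.** The Results section of the protocol article commits to one effectiveness analysis: "Repeated-measures ANOVA or its non-parametric variants will be used after exploring the model assumptions to assess the effectiveness of the intervention". The sentence before it treats the summary measure the same way: "Mean/median and standard deviation/inter-quartile range will be analyzed after exploring skewness for the quantitative variables". Regression is mentioned only as an option: "Regression models may be used for adjustment of covariates to account the confounding factors and for unbiased treatment effect".

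The abstract, under Methods, has no alternative: "Repeated measures ANOVA will be used to analyze the effect of the intervention".

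Under Outcomes, "AHI and ESS will be the primary outcomes". Under Study design, "All outcomes will be assessed at baseline and at the end of 12 weeks", and then "Additionally, a follow-up will occur at the end of 24 weeks with assessment of daytime sleepiness, sleep quality, and breathing pattern dysfunction". AHI is not among the week-24 assessments listed there, so it has two planned measurements, while ESS (daytime sleepiness) has three. The HSAT section defines AHI as "the average number of events of apnea and hypopnea per hour during sleep", a rate that cannot be negative.

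**The concern.** The trial has two parallel arms, so its question is how the arms differ. Repeated-measures ANOVA compares means and a rank method compares orderings. Under the Results wording, which of these is estimated is settled only after the outcome data have been inspected, and the same holds for mean against median. A reader of the final report could not tell from the plan which effect measure was intended.

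There is a second, conditional problem. Some common rank counterparts of repeated-measures ANOVA, namely the Friedman test and, for two visits, the Wilcoxon signed-rank test, have no arm factor. Applied arm by arm, they show whether each arm changed and not whether the arms differ. Both arms receive CPAP and oropharyngeal exercises, so improvement in both is plausible. A significant fall in one arm beside a non-significant fall in the other could then be mistaken for a treatment effect. Nothing in the Results section rules this out.

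**Working it through.** **1. The plan's own figure.** The sample size section gives 116.25 from an effect size of 0.30, 5% significance, 80% power, 20% drop-out and a design effect of 1.5. Working back: 116.25 × 0.80 / 1.5 = 62. A between-groups repeated-measures ANOVA with f = 0.30, two groups, m = 3 measurements and within-person correlation ρ = 0.5 has noncentrality f²·N·m / [1 + (m − 1)ρ]. At N = 62 this is 0.09 × 62 × 3 / 2 = 8.37 on 1 and 60 degrees of freedom, and 62 is the smallest even N that reaches 80% power. Then 62 × 1.5 / 0.80 = 116.25 exactly. The values m = 3 and ρ = 0.5 are inferred, not stated. The match suggests, without proving it, that a between-arm test was in mind.

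**2. Within-arm reading, by formula.** Suppose both arms have the same true change, are independent, and each within-arm test has power p. Exactly one test is significant with probability 2p(1 − p):

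| p | 2p(1 − p) |
|---|---|
| 0.30 | 0.42 |
| 0.50 | 0.50 (maximum) |
| 0.70 | 0.42 |
| 0.80 | 0.32 |
| 0.90 | 0.18 |
| 0.95 | 0.095 |

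**3. Within-arm reading, by simulation.** The assumptions, none of them from the documents, are lognormal AHI with median 14, log-SD 0.5 and correlation 0.5. There were 47 per arm (59 × 0.8 = 47.2) and 3,000 runs per scenario, with a signed-rank test in each arm.

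| Equal true fall in both arms | Significant in one arm only | Significant in both arms |
|---|---|---|
| none | 9% | 0.2% |
| 10% | 39% | 7% |
| 15% | 51% | 28% |
| 20% | 31% | 66% |
| 30% | 1% | 99% |

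This agrees with step 2. At a 20% fall, for example, p ≈ 0.657 + 0.306/2 = 0.81, and 2 × 0.81 × 0.19 = 0.31.

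**4. Does the switch inflate type I error?** In the five equal-change scenarios, a Shapiro-Wilk check on change scores rejected normality in 67-81% of runs, so under this assumed distribution the fallback would often be used. With Mann-Whitney on change as the fallback, the two-stage rule had a false-positive rate of 4.8-5.1%. ANCOVA on log AHI, fixed in advance, had 4.5-5.4%. No inflation is visible.

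**5. What a fixed baseline-adjusted analysis gains.** With equal variance σ² at both visits, a change score has variance 2σ²(1 − ρ). The week-12 value adjusted for baseline has residual variance σ²(1 − ρ²). The ratio is (1 + ρ)/2: 0.65 at ρ = 0.3, 0.75 at ρ = 0.5 and 0.85 at ρ = 0.7. With two visits, the arm-by-time interaction in repeated-measures ANOVA is the change-score comparison, so the gain applies directly to AHI.

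**The case against.** The strongest reply has four parts.

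- **No within-arm test is named.** A reader might infer that skewed AHI will be judged within arms only, because the best-known rank variant has no arm factor. The documents do not support this. They name neither the Friedman nor the signed-rank test, they write of variants in the plural, and they tie the analysis to the effectiveness of the intervention in a parallel-group trial. Rank methods with an arm-by-time test exist, such as the Brunner-Langer statistic and the aligned rank transform. With AHI measured twice, the direct rank counterpart of the interaction test is Mann-Whitney on change, which compares arms. This part stands. It is weaker for ESS, where three visits leave the rank counterpart less determined.
- **Two chances at significance.** A reader might infer that switching tests inflates error. The text selects on model assumptions and not on p-values, and step 4 shows no inflation with a between-arm fallback. This part stands too.
- **The percentages are conditional.** The documents give no AHI distribution beyond the entry range of 5 to 30, and no within-arm power. If both arms fall strongly, the false-difference probability is near zero. This also stands.
- **The detail may be in an analysis plan that is not shown.** This stands only in part. The missing test name and trigger may be excused for that reason. But the article does more than omit detail: it states that the choice follows inspection of the data. An analysis plan that named one test in advance would depart from that sentence.

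**Conclusion.** The point holds in a limited form. The Results section makes both the primary method and the summary measure depend on the observed data, and the abstract does not mention the alternative. The effect measure for AHI and ESS is therefore not settled before the data are seen. That much rests on the text alone.

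Within-arm judgement is a risk that the wording leaves open and not something the plan states. Its size, at most 50% and about 1% for an equal 30% fall, applies only if the fallback is run arm by arm and significance in one arm only is then read as efficacy. The simulated figures also rest on the assumed lognormal AHI. Inflation of type I error by the switch itself is not shown. The sample size is not affected.

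**What to change.** Replace the data-driven switch in the Results section with one prespecified between-arm analysis for each primary outcome: the week-12 value adjusted for its baseline, by ANCOVA or an equivalent mixed model, reported with a 95% CI.

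For AHI, a log scale fixed in advance is an option. If log(AHI + 1) is used, the result is a ratio of AHI + 1 and should be labelled so, because the two ratios differ at low values: AHI of 2 against 1 is a ratio of 2.0, but 3/2 = 1.5 after adding one. Arm means on the original scale should be given beside it.

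Keep rank ANCOVA as a sensitivity analysis, state that within-arm tests do not support efficacy claims, and bring the abstract and the Results section into line.

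The cost is analysis wording. Baseline values are already collected and enrolment stays at 118. The one small downside is that, on a log scale, the main AHI effect is a ratio and not a mean difference.

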### Participant recruitment, sample size, and eligibility criteria

According to the American Academy of Sleep Medicine (AASM) criteria, participants will be diagnosed with OSA by the consultant pulmonologist [16]. The recruitment of the participants will take place at Manipal Hospital, Bangalore, from October, 2023, to February, 2026.

The sample size was calculated at 5% level of significance with 80% power and an effect size of 0.30. The drop-out rate (20%) and the design effect (1.5) were also incorporated. Thus, the sample derived was 116.25 and 118 will be enrolled, with 59 in each group. The eligibility criteria are outlined in Table 1.

**Table 1 Tab1:** Eligibility criteria

Inclusion criteria	Exclusion criteria
Mild and moderate OSA (AHI ≥ 5 to ≤ 30)	Obstructive nasal diseases
Age 25 to 65 years	Craniofacial malformations
Either gender	Comorbid sleep disorders such as insomnia, restless leg syndrome
BMI less than 40 kg/m^2^	Pregnant women
	History of pharyngeal surgery
	History of congestive heart failure, cardiomyopathy, chronic obstructive pulmonary disease, and liver cirrhosis
	History of neuromuscular disorders such as myasthenia gravis, motor neuron disease, and demyelinating diseases
	History of stroke
	Psychiatric illness
	Consumption of alcoholic beverages (more than 3 oz/day or more than 2 alcoholic beverages/day)
	Periodontal disease (gingivitis]
	Temporomandibular joint dysfunction

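### Covariate adjustment is justified as a cure for confounding in a randomised comparison and is not limited to baseline variables; one fixed baseline-adjusted primary model would be sounder and more precise

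*Protocol article*

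**What the plan says.** The Results section names repeated-measures ANOVA, or a non-parametric counterpart chosen once model assumptions have been checked, as the analysis that assesses effectiveness. It then adds: "Regression models may be used for adjustment of covariates to account the confounding factors and for unbiased treatment effect". It names no covariates and does not say how the adjusted result stands in relation to the ANOVA. Missing data are to be handled by intention to treat.

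Under Randomization, allocation, and blinding: "The randomization will be done using computer-generated block randomization". Allocation is concealed in numbered opaque envelopes.

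Two process variables are recorded during the 12 weeks of treatment. For CPAP, given in both arms, "CPAP data will be noted to record compliance". For the exercises, "A weekly exercise diary will be provided to the patients to document their adherence to treatment". Neither is named as a covariate.

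Under Study design, every outcome is measured at baseline and week 12. The week-24 follow-up covers sleepiness, sleep quality and breathing pattern. AHI therefore has two time points and ESS has three.

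**The concern.** Confounding is the problem adjustment solves in an observational comparison. Here the arm is assigned at random and concealed, so baseline factors differ between arms only by chance, and the test's standard error already allows for that. Describing regression as the route to an unbiased effect gives adjustment a role it does not have in this design.

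The rationale matters because it can steer the choice of covariates. An analyst told to look for confounders may look for variables that differ by arm. Beyond chance imbalance, the variables that can differ systematically between randomised arms arise after randomisation, and this trial records two of them. The sentence does not rule them out. Conditioning on a consequence of treatment can remove part of the effect or introduce bias through causes that the variable shares with the outcome.

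The stated rationale also overlooks the real benefit of adjustment, which is a more precise estimate from baseline values already being collected.

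**Working it through.** **1. The plan's own figure.** The section on sample size states: "The sample size was calculated at 5% level of significance with 80% power and an effect size of 0.30", followed by "The drop-out rate (20%) and the design effect (1.5) were also incorporated". Reading 0.30 as Cohen's f for the between-group F test, with 2 groups and an assumed 3 time points and correlation of 0.5, the required total is 61, or 62 for equal arms. Then 62 × 1.5 / (1 − 0.20) = 116.25, which is the stated figure. The calculation contains no covariates, so this point leaves the 118 unchanged.

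**2. Precision gained by adjusting for baseline.** Assume equal variance σ² at baseline and week 12, correlation r between them, and n per arm. The plan does not say which ANOVA term carries the comparison; I take group-by-time. With two time points, as for AHI, that is the test of change scores.

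- Change score: variance of the arm difference = (2/n) × 2σ²(1 − r).
- Baseline-adjusted model: variance ≈ (2/n) × σ²(1 − r²).
- Ratio = (1 − r²) / [2(1 − r)] = (1 + r)/2.

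| r (assumed) | Variance ratio | Standard-error ratio |
|---|---|---|
| 0.3 | 0.65 | 0.81 |
| 0.5 | 0.75 | 0.87 |
| 0.7 | 0.85 | 0.92 |

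The documents give no r, so this is a range and not an estimate.

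**3. What adjusting for a post-randomisation variable could do.** Take no true effect on the outcome. Adherence is A = a·T + 0.5U + error and the outcome is Y = 0.5U + error, where T is the arm, U is an unmeasured shared cause with variance 1, and each error has variance 0.75. Within arm, the slope of Y on A is 0.5 × 0.5 / (0.25 + 0.75) = 0.25, so the adjusted arm coefficient is −0.25a.

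| Arm shift in adherence, a | Bias by formula (SD) | Bias by simulation (SD) | Rejection rate, N = 118 |
|---|---|---|---|
| 0 | 0 | 0.00 | 5.1% |
| 0.3 SD | −0.075 | −0.08 | 7.1% |
| 0.5 SD | −0.125 | −0.12 | 10.4% |

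The loadings of 0.5 and the shifts are assumptions. If the arm does not shift adherence, there is no bias in this model.

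**4. What choosing by result could do.** Null simulations used 6,000 runs for one outcome at the two-sided 5% level, with a baseline–outcome correlation of 0.5 and four weak baseline covariates (all assumed). N = 94 is 80% of 118.

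| Reporting rule | N = 118 | N = 94 |
|---|---|---|
| One fixed analysis (change score) | 4.9% | 5.3% |
| Smaller p of change score and baseline-adjusted | 6.7% | 7.8% |
| Smallest p of change score and any subset of the four covariates added to baseline | 11.9% | 13.5% |

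Monte Carlo error is about 0.3 to 0.4 points. The last two rows require selection by p-value, which the protocol does not describe.

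**The case against.** The defence has four good arguments.

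- **The target is not named.** The text says covariates, no more. CPAP data and the diary are there to document compliance. An ordinary reading is chance imbalance in baseline factors. A reader might infer that the plan will adjust for CPAP use or adherence; nothing in the protocol says so. This stands, and the bias in step 3 is only a possibility that the wording leaves open.
- **The verbs differ.** The ANOVA will be used and regression may be used, which reads naturally as a main analysis with an optional supplement. Reported that way, adjustment causes no inflation. A reader might also infer that regression is to be decided after looking at the data, but the exploring in that section governs the summary statistics and the choice between ANOVA and its non-parametric variant. This stands too, so the rates in step 4 cannot be laid to the plan.
- **The details may sit elsewhere.** A covariate list is commonly left to a full protocol or SAP, and neither is shown. Its absence is not part of this point. What remains is a stated rationale that is wrong for the design, and a covariate list elsewhere would not correct it.
- **Drop-out.** The plan allows for 20%, and randomisation does not guarantee an unbiased comparison of completers. Adjusting for baseline predictors of drop-out can help. That is true, but the sentence speaks of confounding, not missing data, and this argument also calls for baseline variables only.

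**Conclusion.** The point holds in a limited form. The stated reason for adjustment is wrong for a concealed randomised trial, and the sentence does not confine covariates to baseline. A better method is available at no cost in data: one fixed model adjusted for the baseline value of each primary outcome. Its gain over a change-score analysis is a variance ratio of 0.65 to 0.85, or a standard error about 8% to 19% smaller, given equal variances and r between 0.3 and 0.7.

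The documents do not support the stronger conclusions that the plan yields a biased effect or exceeds its 5% level. Bias needs adjustment for a post-randomisation variable that the arm changes. Inflation needs the result to be chosen by its p-value. The protocol states neither. This is an improvement worth making, not a flaw that invalidates the analysis.

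**What to change.** Amend the repeated-measures ANOVA sentence and the regression sentence together. Changing only the second would leave two primary analyses side by side. Suggested content:

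- The single primary comparison of AHI, and of ESS, at week 12 is the arm difference from a model adjusted for the baseline value of that outcome, plus any other baseline covariates fixed in advance, whatever imbalance is observed.
- The unadjusted difference is a sensitivity analysis. Repeated-measures ANOVA or its non-parametric variant, if kept, is labelled as supporting.
- No variable measured after randomisation, including CPAP use and exercise adherence, enters the model for the treatment effect. Both are summarised by arm.
- The references to confounding and to obtaining an unbiased effect are deleted.

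This does change the primary analysis, so it should be dated and made before outcome data are seen by arm. It needs no new data, visits or patients, and the sample size stays at 118. The only loss is the freedom to choose covariates later.
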